**Figure 1 fig1:**
[figure not shown]
Flow chart of the study process.

### Subjects recruitment

2.2

Patients with chronic tinnitus as well as healthy volunteers will be recruited from the Third Affiliated Hospital of Zhejiang Chinese Medical University’s departments of neurology, otolaryngology, and acupuncture and moxibustion.

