#### Exclusion criteria

2.3.2

1) Drug addiction, alcoholism, and mental illnesses (including comprehension difficulties, full aphasia, and severe cognitive disorders);2) Serious systemic illnesses, such as cardiovascular or cerebrovascular disease, or severe abnormalities of the central nervous system; these conditions will be identified through the participant’s self-report during the screening interview and, upon the participant’s consent to access existing medical records, confirmed by medical records or previous diagnostic imaging studies.3) A history of craniocerebral trauma or other documented organic neurological abnormalities;4) Abnormal tympanometric findings, acoustic reflection test findings, otoscopic examination findings or abnormal DPOAEs;5) Ménière’s disease, otosclerosis, acoustic neuroma, abrupt sensorineural hearing loss, conductive and mixed hearing loss, or other conditions affecting the inner ear or auditory nerve;6) History of objective tinnitus, somatosensory tinnitus, external ear canal infection, acute or chronic otitis media, or other conditions affecting the outer or middle ear;7) Participants who are currently receiving or have recently received other tinnitus-related interventions, including pharmacological treatment, sound therapy, psychological interventions, or other acupuncture treatments;8) Unable to tolerate acupuncture treatments due to various reasons, as well as pregnant and lactating women.

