#### Exclusion criteria

2.4.2

1) Pregnant or breastfeeding women, and those who have a request for childbearing within the next 6 months;2) History of head trauma, or history of persistent tinnitus (defined as tinnitus lasting >5 min, occurring more than once per week, or lasting >3 months);3) Abnormal tympanometric findings, acoustic reflection test findings, otoscopic examination findings or abnormal DPOAEs;4) Any condition that precludes ABR testing, such as the existence of metallic implants in the body;5) Participation in any ongoing interventional clinical trials.

If a person satisfies all inclusion requirements and none of the exclusion requirements, they will be qualified to take part in the study. Written informed consent will be obtained from all participants prior to enrollment. Participants will be informed of the study purpose, procedures, potential risks and benefits, and their right to withdraw at any time without consequence.

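### Controls are recruited from the same departments as patients but without most of the patients' neurological and inner-ear or auditory-nerve exclusions, which may bias the baseline wave V comparison towards the null

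*Protocol article*

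**What the plan says.** Section 2.2 gives one recruitment source for both groups: the "departments of neurology, otolaryngology, and acupuncture and moxibustion" of a single hospital.

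For patients, section 2.3.2 lists three exclusions that bear on the structures behind the ABR:

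- Item 2: "Serious systemic illnesses, such as cardiovascular or cerebrovascular disease, or severe abnormalities of the central nervous system". These are to be identified by self-report at the screening interview and, with the participant's consent, confirmed from records or earlier imaging.
- Item 3: "A history of craniocerebral trauma or other documented organic neurological abnormalities".
- Item 5: Ménière's disease, otosclerosis, "acoustic neuroma, abrupt sensorineural hearing loss, conductive and mixed hearing loss, or other conditions affecting the inner ear or auditory nerve".

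For controls, the nearest entry in section 2.4.2 is item 2: "History of head trauma, or history of persistent tinnitus". The other control exclusions are pregnancy, breastfeeding or planned childbearing; abnormal tympanometry, acoustic reflex, otoscopy or DPOAE findings; conditions that prevent ABR testing; and participation in another trial. The section closes with the rule "If a person satisfies all inclusion requirements and none of the exclusion requirements, they will be qualified to take part in the study".

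Matching is on sex and on age within 3 years (section 2.1). The only planned covariates are hearing thresholds, and these enter only if the audiometric profiles differ (sections 2.1 and 2.8).

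**The concern.** Hypothesis 1 compares ABR in chronic tinnitus with ABR in people whose auditory pathway is taken to be normal. The Introduction places the generators of wave V in the lateral lemniscus and inferior colliculus, and that of wave I in the distal auditory nerve. The conditions screened out of the patients but not out of the controls can affect those same structures.

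If cases are screened more strictly than controls on such conditions, the contrast no longer isolates tinnitus. The Discussion expects longer wave V latency in patients. Controls with delayed conduction would pull the two means together and widen the spread of the paired differences. Neither the matching nor the planned covariates would correct this, because neither addresses neurological status.

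The planned effect is small: 0.08 ms against an SD of the paired differences of 0.14 ms. A few affected controls could therefore matter.

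**Working it through.** **1. The two lists side by side**

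| Condition | Patients (2.3.2) | Controls (2.4.1, 2.4.2) |
|---|---|---|
| Head trauma | excluded (item 3) | excluded (item 2) |
| Other organic neurological abnormality | excluded (item 3) | not listed |
| Cardiovascular or cerebrovascular disease, severe CNS abnormality | excluded (item 2) | not listed |
| Inner-ear or auditory-nerve disease | excluded (item 5) | not listed by diagnosis |
| Audiogram, DPOAEs, tympanometry, otoscopy, acoustic reflexes | must be normal | must be normal |

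Control exclusion 4 covers conditions that prevent the ABR test, not conditions that alter its result. A control remains eligible with CNS or cerebrovascular disease, or with another documented neurological or inner-ear/auditory-nerve condition, provided the tests in the last row are normal.

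**2. The plan's own power setting**

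Inputs from section 2.9: mean paired difference 0.08 ms, SD of differences 0.14 ms, two-sided α 0.05, 80% power, 30 pairs required, 36 recruited.

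Standardised difference: 0.08 / 0.14 = 0.571. An exact paired t-test (noncentral t) needs 27 pairs for 80% power, so the stated 30 is not reproduced. It is larger than its inputs require, with power of 85.6% at 30 pairs. At 36 complete pairs, power is 91.5%. Nothing below depends on the gap between 27 and 30.

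**3. Effect of affected controls**

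Let a share f of controls have wave V delayed by D ms. Section 2.8 averages the two ears, so D is the delay in that average; a one-sided delay must be twice D in the affected ear. Then

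- mean difference = 0.08 − f·D
- SD = √(0.14² + f(1 − f)D²)

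The documents give neither f nor D. Both are assumed, and a range is shown for 36 complete pairs:

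| f | D (ms) | Mean difference (ms) | SD (ms) | Power |
|---|---|---|---|---|
| 0 | – | 0.080 | 0.140 | 91.5% |
| 1/36 | 0.2 | 0.074 | 0.144 | 85.5% |
| 1/36 | 0.3 | 0.072 | 0.148 | 80.4% |
| 5% | 0.3 | 0.065 | 0.155 | 69% |
| 10% | 0.3 | 0.050 | 0.166 | 42% |

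Worked example, f = 10% and D = 0.3: mean = 0.08 − 0.03 = 0.05; SD = √(0.0196 + 0.09 × 0.09) = √0.0277 = 0.166; ratio 0.300; power 42%.

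**4. The longitudinal analysis**

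A stable delay D is present in a control at both T0 and T1. The change is (T1 + D) − (T0 + D) = T1 − T0, so D cancels from the group × time contrast. For the ICC, a stable delay in a few controls adds between-person variance, which does not lower it.

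**The case against.** **The shared screens do real work.** Controls must have normal tympanometry, otoscopy, DPOAEs and acoustic reflexes as well as a normal audiogram. Section 2.5 tests reflexes ipsilaterally and contralaterally at four frequencies, so the auditory nerve and part of the brainstem pathway are probed. Many otological cases and some auditory-nerve cases would be removed. This stands and narrows the gap. What remains is mainly neurological disease with normal hearing and normal reflexes.

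**The group is called healthy throughout.** Section 2.2 does not say that the volunteers are patients of those departments; they could be staff or companions. Table 1 schedules a medical history at enrolment. This lowers the likely number of affected controls. It does not close the gap: the article does not define healthy beyond the two lists, the closing sentence of section 2.4.2 makes those lists decisive, and the self-report and record check is written only into the patient list.

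**The study calls itself exploratory, and a bias towards the null cannot create a false finding of wave V prolongation.** That is fair. It limits the consequence to a missed or understated difference.

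**Stronger readings.** A reader might infer that the comparison is certainly biased, that the control ICC and the group × time reference are spoiled, or that every patient exclusion should be copied across. The documents support none of these. The bias depends on who enrols. A stable delay largely cancels in the longitudinal contrast and does not lower the ICC. Patient exclusions 1 and 6 are already partly covered by the controls' cognition and language requirement, their ear screens and their tinnitus exclusion.

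**Conclusion.** The point holds as an asymmetry in the printed eligibility rules. It is not a detail lost when the protocol was condensed, because both lists appear and are declared sufficient. Of patient exclusions 2, 3 and 5, only head trauma carries over to controls drawn from the same departments.

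The consequence is a possible bias, confined largely to the baseline wave V comparison of Hypothesis 1 and probably towards the null. Its size cannot be read from the documents. Under the assumed range, power at 36 complete pairs runs from 85.5% (one control delayed 0.2 ms) to 42% (10% delayed 0.3 ms), against 91.5% with none. With a single affected control at 0.3 ms, power is 80.4%, still at the planned level, so the harm becomes serious only if several such controls enrol. The illustration also assumes that the pilot values of 0.08 and 0.14 ms hold and that the affected controls have longer, not shorter, latencies.

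**What to change.** Before enrolment, add patient exclusions 2, 3 and 5 of section 2.3.2 to the control list in section 2.4.2, with the same self-report and, with consent, the same check of medical records. The medical-history item that Table 1 already schedules at enrolment can carry this, so no new visit or test is needed.

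The cost is one eligibility amendment and a few more screen failures among volunteers. Timing matters: once controls have been enrolled under the looser list, the planned matching and covariates cannot restore comparability.

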### Inclusion and exclusion criteria of tinnitus patients

2.3

#### Inclusion criteria

2.3.1

1) Diagnosis of bilateral chronic subjective tinnitus (including primary and secondary tinnitus, as well as cochlear and central cases), with a duration of at least 6 months, and a score of at least 16 on the Chinese version of the THI scale (mild) (30);2) Pure-tone average hearing threshold (PTA) < 20 dB HL in both ears, with no individual frequency exceeding 30 dB HL (31);3) Normal tympanometric findings, acoustic reflection test findings, sotoscopic examination findings and normal Distortion product otoacoustic emissions (DPOAEs);4) Aged between 18 and 60 years, inclusive, any sex;5) Both tympanic membranes are intact and the external auditory canal is clear;6) Sufficient expressive and comprehensive language skills, adequate cognitive function, and the capacity to collaborate with the study’s experimental procedures;7) Signing the informed consent form and not taking part in any other interventional clinical trials at this time.

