
**Table 1 tab1:** SPIRIT schedule of enrollment, interventions, and assessments.

	Study period							
	Enrolment	Allocation	Treatment period				Post-treatment	Follow-up
TIMEPOINT (week)	Week −1(T0)	Week 0	W1	W2	W3	W4	W5 (T1)	W13 (T2: 8-week FU)
Enrolment								
Eligibility screen	X							
Informed consent	X							
Demographic/medical history	X							
Allocation		X						
Interventions								
Acupuncture (10 sessions, 3×/week)			X	X	X	X		
Assessments								
ABR parameters	X						X	
Pure-Tone Threshold testing	X							
Tympanometry & Acoustic reflex testing	X							
DPOAEs	X							
Otoscopic examination	X							
THI	X						X	X
TEQ	X						X	X
Loudness/Annoyance VAS	X						X	X
Adverse events			X	X	X	X	X	

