### Outcome measures

2.7

The outcomes of this study were designed to evaluate both the clinical efficacy and neurophysiological changes associated with acupuncture treatment in patients with chronic tinnitus. Considering the different characteristics of subjective symptom assessment and electrophysiological evaluation, clinical and neurophysiological outcomes will be analyzed separately.

The assessment schedule is summarized in Table 1. Patient-reported outcomes, including tinnitus severity and related functional impairment, will be assessed at baseline (T0), after completion of acupuncture treatment (T1), and at the 8-week (after the beginning of acupuncture treatment) follow-up visit (T2). Auditory brainstem response (ABR) measurements will be performed in both the healthy control group and the tinnitus patient group at baseline (T0) and after treatment completion (T1), as the primary purpose of the electrophysiological assessment is to evaluate changes in auditory pathway function during the course of treatment. ABR testing will not be conducted at the follow-up visit, as the primary purpose of the follow-up assessment is to evaluate the durability of subjective tinnitus improvement.

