##### Primary clinical outcome

2.7.1.1

The primary clinical outcome will be the change in the Tinnitus Handicap Inventory (THI) score from baseline to post-treatment and follow-up.

The THI is a quick, simple, and psychometrically sound tool that assesses how tinnitus affects day-to-day functioning. The THI has 25 questions with three main subscales (affective, functional, and severity scores) and a total scale score of 0–100, with lower scores indicating less severe tinnitus-related handicap. It has been shown to be an accurate and significant indicator of self-reported tinnitus-related discomfort (38).

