Clinical outcomes, including THI, TEQ, and tinnitus-related VAS scores, will be evaluated only in tinnitus participants using one-way repeated-measures ANOVA across baseline, post-treatment, and 8-week follow-up. When assumptions of normality or sphericity are violated, appropriate non-parametric tests or Greenhouse–Geisser corrections will be applied. Associations between changes in ABR parameters and changes in subjective tinnitus severity will be explored using Spearman rank correlation analysis. For secondary analyses involving multiple ABR parameters, false discovery rate (FDR) correction using the Benjamini-Hochberg procedure will be applied to control for multiple comparisons.

Missing data will be assessed and reported. Linear mixed-effects models or multiple imputation methods will be considered for sensitivity analyses if substantial missing longitudinal data occur.

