
### Limitations and future directions

3.1

This study has a number of limitations. Its sample size is comparatively modest because it is a single-center study. Therefore, the results may not be fully extended to a wider range of people with tinnitus. Another limitation is that the intervention group did not include a tinnitus control group receiving sham treatment, making it impossible to compare the effects of true acupuncture and sham acupuncture on patients with tinnitus. This is particularly worthy of attention, because the 2024 VA/DOD guidelines found insufficient evidence of acupuncture, and thus emphasized the need to carry out good controlled trials. While the self-controlled design allows each patient to serve as their own control and reduces between-subject variability, it cannot fully distinguish specific acupuncture effects from placebo effects, regression to the mean, or non-specific treatment effects. Although the inclusion of a healthy control group with repeated ABR measurements helps quantify normal test–retest variability, it does not replace a parallel sham-controlled arm. Therefore, our findings should be interpreted as preliminary and hypothesis-generating. Future adequately powered, sham-controlled randomized trials are needed to definitively establish the efficacy of acupuncture for chronic tinnitus. Third, the ABR protocol in this study uses broadband click stimuli rather than frequency-specific tone bursts. While this choice ensures clinical standardization and comparability with previous literature, it may reduce the sensitivity to detect frequency-specific cochlear synaptopathic changes that have been suggested to underlie some forms of tinnitus (51). Future studies incorporating multiple frequency-specific stimuli (e.g., 1, 2, and 4 kHz tone bursts) would provide a more comprehensive assessment of the relationship between acupuncture, ABR parameters, and tinnitus pathophysiology. Fourth, this study employs an assessor-blinded design rather than a double-blind design. Due to the nature of the acupuncture intervention, neither patients nor acupuncturists can be blinded to treatment allocation, which may introduce performance bias and expectation effects. To mitigate this, we have implemented several measures which have been motioned in the Design overview section. Nonetheless, we acknowledge that the lack of patient blinding remains a limitation. Fifth, treatment adherence is currently assessed primarily by session attendance, which does not fully capture treatment fidelity. To strengthen this aspect, all acupuncturists will follow a detailed Standard Operating Procedure (SOP) manual, needle manipulation parameters (angle, frequency, and duration) will be recorded for each session, and the De Qi sensation will be assessed using the C-MASS scale after each session. These additional measures will allow us to characterize the consistency of treatment delivery beyond simple attendance records. In addition, although ABR measurement is valuable for evaluating brainstem function, it cannot capture changes in the cortical level, which may also affect the perception of tinnitus. Lastly, this study did not set up a long-term follow-up beyond the treatment period, so it is impossible to evaluate whether the observed effect is persistent. And the 8-week follow-up assessment was conducted by telephone, which may introduce recall bias and reduce the accuracy of symptom evaluation compared with face-to-face assessment.

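### As scheduled, the screening THI (at least 16 for entry) appears to double as the baseline of the primary THI change, adding a small, avoidable regression-to-the-mean fall in the favourable direction

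*Protocol article*

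**What the plan says.** - **Entry (2.3.1).** Patients need "a score of at least 16 on the Chinese version of the THI scale (mild"), a one-sided lower limit on a scale that section 2.7.1.1 describes as "a total scale score of 0–100, with lower scores indicating less severe tinnitus-related handicap".
- **Schedule (Table 1).** The row "Eligibility screen" is marked at Week −1 (T0). The THI row is marked at Week −1 (T0), W5 (T1) and W13 (T2). The Week 0 column has an entry for allocation but none for THI, so only one THI precedes treatment.
- **Baseline (2.7).** Patient-reported outcomes "will be assessed at baseline (T0), after completion of acupuncture treatment (T1") and again at follow-up (T2).
- **Primary clinical outcome (2.7.1.1).** It is "the change in the Tinnitus Handicap Inventory (THI) score from baseline to post-treatment and follow-up".
- **Analysis (2.8).** Clinical scores "will be evaluated only in tinnitus participants using one-way repeated-measures ANOVA across baseline, post-treatment, and 8-week follow-up". Section 2.1 states that there is no sham group. Healthy controls are retested on ABR only, so nothing in the study estimates how THI moves without treatment.
- **Acknowledged limit (3.1).** Of the self-controlled design, the article says that "it cannot fully distinguish specific acupuncture effects from placebo effects, regression to the mean, or non-specific treatment effects".

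**The concern.** A lower limit on a score with measurement error and day-to-day fluctuation lets in some patients whose score happened to be high that day. It keeps out some whose score happened to be low. If the same score is then the baseline, the group's next score falls on average with no treatment effect. A fall in THI is the result that Hypothesis 2 looks for, so the bias favours the hypothesis, and no comparator is available to subtract it.

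The general disclosure in 3.1 covers what any uncontrolled pre-post design suffers. It does not connect regression to the mean with the entry cut-off, and no design or analysis step limits it. The blinding measures in 2.1 cannot remove an effect of selection on the baseline. Using one score for two purposes is a separate choice from having no sham arm, and it is cheap to avoid.

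**Working it through.** The plan gives no figure for this effect, so there is none to reproduce. Its sample-size inputs (2.9) serve as the yardstick: anticipated THI reduction 12.07, SD 23.28, target 36 patients, attrition 20%.

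**Step 1: expected fall with no treatment effect.** For a normally distributed score with mean μ, SD σ and retest correlation r, selected at 16 or more:

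fall = σ × (1 − r) × φ(z) / (1 − Φ(z)), with z = (16 − μ)/σ

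The documents give none of μ, σ or r. The values below are assumptions: μ 25–40, σ 20–22, r 0.8–0.9.

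| μ | σ | r | z | φ(z)/(1 − Φ(z)) | Fall (points) | Share of 12.07 |
|---|---|---|---|---|---|---|
| 40 | 20 | 0.9 | −1.200 | 0.1942/0.8849 = 0.219 | 20 × 0.1 × 0.219 = 0.44 | 4% |
| 40 | 22 | 0.8 | −1.091 | 0.2200/0.8623 = 0.255 | 22 × 0.2 × 0.255 = 1.12 | 9% |
| 25 | 22 | 0.8 | −0.409 | 0.3669/0.6588 = 0.557 | 22 × 0.2 × 0.557 = 2.45 | 20% |

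The range is about 0.4 to 2.5 points.

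**Sensitivity of Step 1.** With r = 0.7, μ = 25 and σ = 22 the fall is 3.7. With μ = 50, σ 20–22 and r 0.8–0.9 it is only 0.2–0.6. Over a much wider grid (μ 20–50, σ 18–25, r 0.6–0.9) it runs from 0.1 to 7.0, with 1.4 points (12% of 12.07) at μ = 40, σ = 22, r = 0.75.

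**Step 2: effect on the error rate.** This uses the baseline to post-treatment contrast as a paired t-test, which is the framework of 2.9. The analysis in 2.8 is a three-time-point ANOVA, so these rates are a guide to that analysis and not its exact error rate.

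- Standard error at n = 36: 23.28/√36 = 3.88.
- Non-centrality: 1/3.88 = 0.258 for a 1-point bias and 2/3.88 = 0.515 for 2 points, with 35 degrees of freedom.
- Two-sided rejection at nominal 5%: 5.7% for 1 point and 7.9% for 2 points.
- With 20% attrition (36 × 0.8 = 28.8, about 29 completers; standard error 23.28/√29 = 4.32): 5.6% and 7.3%.

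The SD of 23.28 is the plan's own figure for change after treatment. The assumptions in Step 1 imply a smaller SD for untreated change, and a smaller SD would raise these rates. For example, at μ = 40, σ = 22, r = 0.75 and 29 completers, the rate is 6.1% with SD 23.28 and 7.7% with the implied SD of 15.2.

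**Step 3: with a separate baseline.** If the baseline THI is taken after screening, and errors are independent between visits with equal correlation between all visits, selection on the Week −1 score lifts baseline and post-treatment scores equally. The part of the change caused by the cut-off is then about 0.

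**The case against.** - **It is disclosed, and the claims are limited.** The article names regression to the mean, calls the findings preliminary and hypothesis-generating, and defers efficacy to sham-controlled trials. A reader might infer that the bias is hidden or that it invalidates the THI result. The documents support neither. What stands is that one component could be reduced cheaply and is not.
- **The size is assumed.** A cut-off of 16 on a 0–100 scale excludes few patients if the clinic's mean is well above it. The 2.5-point end needs an unselected mean of 25, at which about a third of candidates would fail the cut-off, and no section supports that for patients recruited from hospital departments. This stands, and the effect may be at the low end.
- **The favourable tail alone looks worse.** A reader might cite a rise from 2.5% to 4.4% (1 point) or 7.2% (2 points). Section 2.8 specifies two-sided tests, so 5.7% and 7.9% are the relevant rates.
- **The double use is not stated in words.** It is read from Table 1, and a full protocol may separate the two administrations. The article's schedule, however, shows no second pre-treatment THI.
- **The fix is partial.** If THI errors persist over a week, part of the bias remains. It also moves the THI baseline away from the ABR baseline. Both points stand and are costed under the fix.

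**Conclusion.** The point holds as a modest, cheaply avoidable bias. The direction follows from the documents: a one-sided entry limit on the outcome scale, a single scheduled pre-treatment THI and no THI comparator. The size does not. Under the stated assumptions it is about 0.4–2.5 points, 4%–20% of the planned 12.07. A 1- to 2-point bias takes the two-sided rejection rate under no effect from 5% to about 5.7%–7.9% at n = 36.

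It would be wrong to conclude that a 12-point fall could be mainly regression caused by the cut-off: even the widest grid tops out at 7.0 points, and only with a low mean, a large SD and a low retest correlation. It would also be wrong to conclude that removing this part makes the THI change attributable to acupuncture.

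**What to change.** 1. In Table 1, keep the Week −1 THI for eligibility only and add a THI at Week 0, before the first session.
2. In 2.7.1.1, define the Week 0 score as the baseline for the primary change, and align the T0 definition for THI in 2.7.
3. Report the Week −1 to Week 0 change descriptively. It mixes the selection effect with one week of drift and should not be presented as a clean estimate of untreated drift.
4. For the correlations between ABR change and THI change (2.8), add a sensitivity analysis with the Week −1 THI, because baseline ABR stays at Week −1.

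**Cost.** One more 25-item questionnaire per patient, in a column that Table 1 already has; a possibly smaller THI effect; and a one-week gap between the ABR and THI baselines. Some bias remains if THI errors are correlated across that week. Placebo response and natural course are untouched, so the limitation in 3.1 should stay.
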